### Sheehan disability scale (SDS)

The SDS [49] is a brief self-report measure that was developed to assess functional impairment in three inter-related domains: work/school, social and familiy life. The patient rates the extent to which problems in these areas are present on a 10 point visual analogue scale and can thus be used to measure functioning.

### Statistical analyses

All analyses will be executed using SPPS for Windows version 18.0. Frequency tables will be provided for all baseline, end of treatment and follow-up variables. Descriptive statistics will include mean, median, interquartile range, numbers and percentages of patients, as appropriate. If applicable, 95% confidence intervals will be given. To compare differences between groups (Seeking Safety vs CBT) *t*-test or mann whitney U tests will be used in case of continuous variables, as appropriate. For categorical variables chi-squared tests will be used. Repeated measures analyses (mixed models in SPSS) will be used to test the differences between the treatment conditions over time in severity of substance use problems as measured by the EuropASI severity score (pre, post and follow-up). The data will be tested for normality and transformed as appropriate when the data are skewed. Analyses will be based on the intent-to-treat principle. Participants have to attend at least one session to be considered part of this group. Differences regarding gender will be analysed and when appropriate, gender will be included in the analyses as a confounder or effect modifier. Multiple Imputation will be used for missing data. Effect sizes will be calculated to facilitate comparison of improvement between the two groups. Linear regression analyses will be used to determine the predictors of change in substance use and trauma symptoms. Also, amount of prior psychiatric treatment will be used in the analysis as a covariate.

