### Sample size calculation

The sample size for this study is calculated using a significance level of 95% (p < 0.05), a power of 80% and the same number of patients in the intervention and control group (ratio = 1).

Primary outcome variable is substance use severity as measured with the EuropASI. In recent studies, conducted within the same institution [34] but with a population of inpatients, a mean baseline score of 5.2 was found for the alcohol domain and 4.0 for the drugs domain. We expect the mean baseline scores for the outpatients to be somewhat lower, however not considerably. For comparison of baseline scores on the EuropASI, see [22,23]. For practical reasons we are using the mean of both domains (alcohol and drugs) for the sample size calculation. Thus, the mean score for substance use severity will be somewhat lower than (5.2 + 4.0)/2 = 4.6 with a standard deviation of 2.7. For this sample size calculation we will use a baseline score of 4.0 with the same standard deviation. We expect the substance use severity to improve with 60% [23] to 1.6 (SD = 2.0) at end-of-treatment for the intervention group and 2.8 (SD = 2.0) for the control group. We used PS – Power and Sample Size Calculation to calculate the sample size, which resulted in a sample size of 45 patients in each group. Drop-out rates for this treatment are available for the past years from a management information system and are estimated around 20%. This drop-out rate may seem low compared to the numbers that are known from previous studies in SUD patients. However, we will use this percentage to calculate the number of patients that are needed, but will perform an analysis on drop-out halfway through the study. When the drop-out rates turn out to be higher than expected, an amendment will be proposed to the medical ethical committee to continue including patients for an extended period of time. Because of the calculated drop-out rate, an extra 9 participants will be included in both the intervention and the control group, yielding a total of 108 participants for the randomized controlled trial. Based on treatment entry numbers from previous years, approximately two years will be needed to include all patients. Furthermore, this number of patients seems plausible considering sample sizes in previous studies that show similarity in design [21,22].

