### Data collection

Patients in both treatment conditions will be assessed identically: at the start of treatment (baseline), at the end of treatment (after three months) and at follow up (six months after start of treatment). Patients will be assessed by research assistants at these time points. Under their supervision patients will fill out most of the questionnaires in an online environment in which the data is linked to their electronic patient file.

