Thirdly, while previous studies on Seeking Safety have mostly been focused on patients with PTSD, in this study patients will also be included if they have experienced a traumatic event and present with some PTSD symptoms, but not necessary with full-blown PTSD. That way, the possible benefits of this treatment will be available for a substantial larger group of patients. A possible limitation of this procedure is that self-reported PTSD-related symptoms will be used to include patients in the study. Because the sample will consist of SUD patients, a proportion of the symptoms they report, may be due to substance use or withdrawal (e.g. sleep problems, difficulties concentrating). The symptoms of hyperarousal could be independent of any traumatic experience. For the purpose of this study, however, this is not a problem. There may be instances where a patient is included in the study while his symptoms are primarily related to substance use, but we still expect this patients to benefit from Seeking Safety in alleviating his symptoms.

The aim of this RCT is to test the efficacy of Seeking Safety versus CBT in an outpatient population of SUD patients. The design of the study is based on the fact that both Seeking Safety and CBT are evidence-based models, but CBT does not address trauma or PTSD. We expect that a majority of the patients may benefit from a treatment that focuses on both trauma and substance use. If the intervention group is more successful in reducing substance use and PTSD symptoms, it can be argued that Seeking Safety should be offered for patients presenting with trauma issues.

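### Only the EuropASI is given a model that uses baseline; the other continuous secondary outcomes are left with a two-group test that is valid but less efficient than it could be at no cost

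*Protocol article*

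**What the plan says.** The Statistical analyses section of the protocol article names two kinds of between-arm analysis for continuous data.

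- A general one: t-tests or "mann whitney U tests will be used in case of continuous variables, as appropriate". The sentence names no outcome and no time point, and does not say whether end values or changes are compared.
- A repeated-measures mixed model for differences between conditions over time "in severity of substance use problems as measured by the EuropASI severity score (pre, post and follow-up"). No other outcome is attached to it.

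The same section names prior psychiatric treatment as a covariate, without saying in which analysis. It allows gender as a confounder or effect modifier where appropriate, and plans linear regression to find predictors of change in substance use and trauma symptoms. None of these is described as adjusting the arm comparison for an outcome's own baseline value.

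That value will exist. Under Data collection, both arms follow one common schedule: "at the start of treatment (baseline), at the end of treatment (after three months) and at follow up (six months after start of treatment"). Under Instruments and outcome, every listed measure other than the primary one is a secondary outcome.

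**The concern.** The article names a method that uses baseline and gives it to one outcome. For SRIP, TSC-33, OCDS, SDS and the UCL subscales, the only named arm comparison is a two-sample test. Such a test leaves in its error term all the between-patient variation that the baseline score could explain.

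PTSD symptoms carry weight in this trial. The Discussion argues for offering Seeking Safety "If the intervention group is more successful in reducing substance use and PTSD symptoms". The PTSD half of that argument would rest on the less efficient test, so a real difference is more likely to be missed than it need be.

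**Working it through.** **1. The plan's own figure.** The Sample size calculation uses "a significance level of 95% (p < 0.05), a power of 80"%, "the same number of patients in the intervention and control group (ratio = 1"), and improvement "to 1.6 (SD = 2.0) at end-of-treatment for the intervention group and 2.8 (SD = 2.0) for the control group". The difference is 2.8 − 1.6 = 1.2 and d = 1.2 / 2.0 = 0.6. Taking the test as two-sided (the text does not say):

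- Normal approximation: n = 2 × (1.960 + 0.842)² × (2.0 / 1.2)² = 43.6, so 44 per arm.
- t-based: 44.6, so 45 per arm, with power 80.4% at 45.

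This reproduces the plan, "which resulted in a sample size of 45 patients in each group". The figure covers the primary outcome only; there is no power figure for a secondary outcome to check.

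**2. Inputs for the secondary outcomes.** From the plan: 45 analysed per arm and a 5% level. Assumed, because the plan gives neither: d = 0.5 and a correlation ρ between baseline and end-of-treatment score of 0.3, 0.5 or 0.7. The change-score column also assumes equal SDs at the two times.

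**3. Formulas.** Power comes from the noncentral t distribution with noncentrality d* × √(45/2) = 4.743 × d*, where d* is:

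- unadjusted end values: d
- baseline-adjusted (ANCOVA): d / √(1 − ρ²)
- change scores: d / √(2 − 2ρ)

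Charging one degree of freedom for the covariate changes the power by no more than about 0.1 point.

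**4. Results at d = 0.5.**

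| ρ | Unadjusted | Change score | Baseline-adjusted | 1 − ρ² | Unadjusted n per arm that 45 adjusted is worth |
|---|---|---|---|---|---|
| 0.3 | 65.0% | 50.9% | 69.1% | 0.91 | 45 / 0.91 ≈ 49 |
| 0.5 | 65.0% | 65.0% | 77.3% | 0.75 | 45 / 0.75 = 60 |
| 0.7 | 65.0% | 85.7% | 90.7% | 0.51 | 45 / 0.51 ≈ 88 |

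The gain over unadjusted end values is 4.1, 12.3 and 25.7 points. Over change scores it is 18.2, 12.3 and 5.0 points.

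**5. Sensitivity to d.** At d = 0.4, unadjusted power is 46.7%, against 50.3%, 58.2% and 74.8% adjusted. At d = 0.6 it is 80.4%, against 83.9%, about 90% and 97.6%. The difference detectable with 80% power falls from 0.60 to 0.57, 0.52 and 0.43 SD.

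**6. SRIP in particular.** The inclusion criteria require a SRIP score of at least 40. That truncates the baseline distribution and may lower ρ, so the ρ = 0.3 row may be nearest for SRIP. The other measures have no direct cut-off of this kind.

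**The case against.** The strongest reply is that the t/Mann-Whitney sentence is generic. It follows the descriptive statistics, could serve baseline comparisons, and does not exclude change scores. Other text points towards change: Study design speaks of measuring change over time on the study's variables generally, and effect sizes are meant to compare improvement. A covariate cannot enter a t-test, so some model must be intended. A condensed article may also leave a secondary-outcome model to a fuller document.

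Part of this stands. A reader might infer that the secondary outcomes will receive only unadjusted tests; the text does not say so. It names no other arm comparison for them, which is a weaker statement. But the point is not merely absent detail: the article states a method for continuous variables and confines the better one to the EuropASI. The change-score reading does not remove the gain, since ANCOVA has higher power at every correlation tabulated.

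Three further inferences fail:

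- That prior psychiatric treatment is the only covariate. Gender is also named, conditionally.
- That EQ-5D is compared without its baseline. The Cost-effectiveness analysis section compares QALYs at baseline and after follow-up.
- That chance baseline imbalance adds false-positive risk. Under randomisation the unadjusted test keeps its 5% level, because such imbalance is already in its standard error. Only precision is at stake.

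It is also fair that the trial is not sized on secondary outcomes, and that the Discussion sentence is an argument, not a decision rule.

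**Conclusion.** The point holds as one of efficiency, not validity. For SRIP, TSC-33, OCDS, SDS and the UCL subscales, the named between-arm method makes no stated use of a baseline that is already collected, and a concretely better method is already planned for another outcome.

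The size cannot be derived from the protocol. With 45 per arm and an assumed d of 0.5, the gain over unadjusted end values runs from about 4 points (ρ = 0.3) to about 26 (ρ = 0.7), and for SRIP it may sit near the bottom of that range. A reader might take the middle or upper figures as the power lost on PTSD symptoms; the documents do not support that, because they give neither ρ nor a PTSD effect size. The direction is safe: any non-trivial correlation gains precision. The change is worth making, but the plan is not wrong without it.

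**What to change.** In Statistical analyses, state that SRIP, TSC-33, OCDS, SDS and the UCL subscales at t = 1 and t = 2 will each be compared between arms with a linear mixed model on the post-baseline values, with terms for arm, visit, arm-by-visit and that outcome's baseline value (or with ANCOVA at each visit), reporting the adjusted mean difference and 95% confidence interval at each visit. Keep t and Mann-Whitney tests for descriptive use. The UCL results can stay exploratory, as the protocol already treats changes in coping style. EQ-5D can stay with the cost-utility analysis.

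The cost is a wording change and one degree of freedom per model for the baseline term. The baseline data are already collected and mixed models in SPSS are already planned, so no extra patients, visits or software are needed.

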**Discussion:**

This study protocol presents a RCT in which the efficacy of an integrated treatment for comorbid PTSD and SUD, Seeking Safety, is evaluated in a SUD outpatient population compared to CBT. It is expected that the intervention group will show significantly more improvement in substance use severity compared to the control group at end-of-treatment and at follow-up. Furthermore, a lower drop-out rate is expected for the intervention group. If the intervention proves to be effective, it can be implemented. A cost-effectiveness analysis will be conducted to evaluate the two treatments.

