### Instruments and outcome

The primary outcome in this study is substance use severity at end of treatment as measured with the EuropASI. This measure will provide a composite score for alcohol and drugs which incorporates the number of days of use in the previous 30 days, amount of money spent on drugs or alcohol, perceived problems and burden of problems associated with substance use. The composite score for alcohol use severity will be used as the primary outcome measure for patients with alcohol use disorder and the composite score for drug use severity will be used for patients with substance use disorder according to the DSM-IV. Secondary outcome measures are the other measures listed below.

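### The primary outcome and sample size are the end-of-treatment difference, but the only analysis tied to EuropASI severity tests differences over three visits, with no end-of-treatment contrast named as primary and no baseline adjustment

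*Protocol article*

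**What the plan says.** Three sections of the protocol article bear on this.

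- **Instruments and outcome** fixes one time point: "The primary outcome in this study is substance use severity at end of treatment as measured with the EuropASI".
- **Sample size calculation** uses the same time point. Severity is expected to fall "to 1.6 (SD = 2.0) at end-of-treatment for the intervention group and 2.8 (SD = 2.0) for the control group". The baseline SD is given in "5.2 + 4.0)/2 = 4.6 with a standard deviation of 2.7" and is kept for the assumed baseline mean of 4.0. The result is 45 per group.
- **Statistical analyses** ties one method to EuropASI severity: "Repeated measures analyses (mixed models in SPSS) will be used to test the differences between the treatment conditions over time". The occasions listed are pre, post and follow-up, so baseline is one of the responses. Prior psychiatric treatment is named as a covariate; baseline severity is not. A separate, general sentence lists t-tests or Mann-Whitney U tests for comparing the arms on continuous variables, without linking them to any outcome.

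The Discussion paragraph of the Abstract states the expectation as "significantly more improvement in substance use severity compared to the control group at end-of-treatment and at follow-up", which covers two time points.

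**The concern.** The outcome and the sample size ask whether the arms differ at the end of treatment. A test of differences over three visits most naturally asks whether the arms' profiles differ anywhere across those visits. The two questions can have different answers: the profile test can be significant because of follow-up alone, or miss a real end-of-treatment difference of the planned size.

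Precision is also at stake. In a model with baseline as an unconstrained response, the pre-to-post interaction contrast is a difference between mean changes, so it carries the larger baseline SD of 2.7. The sample size rests on the end-of-treatment SD of 2.0 alone. Baseline EuropASI is already collected, and adjusting for it would reduce the variance.

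**Working it through.** **Inputs from the Sample size calculation section.** Significance level and power: "using a significance level of 95% (p < 0.05), a power of 80"%. Allocation: "the same number of patients in the intervention and control group (ratio = 1"). End-of-treatment difference 2.8 − 1.6 = 1.2, SD 2.0 in each arm. Baseline SD 2.7. The number of sides is not stated; two-sided is taken because it reproduces the stated size (one-sided gives 35 per arm by the normal approximation).

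**Assumptions not in the article.** The baseline-to-post correlation r and, for the three-visit test, the follow-up SD, the other correlations and the follow-up difference. Ranges are shown.

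**Step 1: reproduce the stated size.** Two-sample t-test, noncentrality 1.2 / (2.0 × √(2/n)). Power is 0.795 at n = 44 and 0.804 at n = 45. The stated 45 is therefore a comparison of end-of-treatment scores with no baseline term.

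**Step 2: pre-to-post difference in change, 45 per arm.** SD of change = √(2.7² + 2.0² − 2r × 2.7 × 2.0) = √(11.29 − 10.8r).

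**Step 3: end-of-treatment difference adjusted for baseline, 45 per arm.** Residual SD = 2.0 × √(1 − r²).

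| Assumed r | SD of change | Power, change | Adjusted SD | Power, adjusted |
|---|---|---|---|---|
| 0.3 | 2.84 | 51% | 1.91 | 84% |
| 0.5 | 2.43 | 64% | 1.73 | 90% |
| 0.6 | 2.19 | 73% | 1.60 | 94% |
| 0.7 | 1.93 | 83% | 1.43 | 98% |
| 0.8 | 1.63 | 93% | 1.20 | over 99% |

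The SD of change equals the planned 2.0 when 7.29 = 10.8r, that is at r = 0.675. There the power is the planned 0.804. Exactly 80% is reached slightly lower, at r = 0.671.

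The ordering of the two methods does not depend on r. The variance of change minus the adjusted variance is (11.29 − 10.8r) − (4 − 4r²) = 7.29 − 10.8r + 4r² = (2.7 − 2r)², which is positive for every possible correlation. At r = 0 the adjusted analysis equals the planned t-test apart from one degree of freedom.

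**Step 4: condition-by-time test on 2 degrees of freedom.** Noncentral F, 45 per arm, SDs 2.7, 2.0 and 2.0, one common correlation r, and a difference of 1.2 at end of treatment:

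| Assumed r | 1.2 at follow-up | 0.6 at follow-up | 0 at follow-up |
|---|---|---|---|
| 0.3 | 48% | 42% | 64% |
| 0.5 | 61% | 55% | 79% |
| 0.6 | 71% | 64% | 88% |
| 0.7 | 82% | 77% | 95% |
| 0.8 | 93% | 90% | 99% |

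Now reverse the pattern: no difference at end of treatment and 1.2 at follow-up. With r = 0.5 between baseline and each later visit and 0.6 between the two later visits, the test rejects about 86% of the time although the primary outcome shows no effect. Under the same correlations, with 1.2 at both visits, it rejects about 60% of the time.

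**The case against.** The strongest defence is that the article does not fix the wrong test. The Statistical analyses section does not call the mixed model primary and does not mention an interaction or a 2-degree-of-freedom test. A three-visit mixed model can produce an end-of-treatment contrast; with complete data and an unconstrained baseline, the arm difference at t = 1 is the raw difference with SD 2.0, exactly what was sized. The general t-test sentence, applied at t = 1, would be the sized test as well. A three-visit model also serves the Abstract's expectation about both time points, and a condensed article may leave the contrast to an analysis plan.

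Most of this stands, and it limits the point. It does not remove it. The sections as written leave two or more candidate tests of the primary outcome with no rule for choosing. The only one attached to EuropASI severity is worded as a test over time, which does not match the single time point defined and sized.

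A reader might go further and infer that the planned test falls below 80% power on the protocol's own SDs. The article does not support that. The SDs 2.7 and 2.0 do not determine the power of a change contrast without r, and no r is given; at 0.7 or 0.8 the contrast exceeds 80%. The three-visit figures depend on still more unstated quantities.

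**Conclusion.** The point holds as a mismatch and as a missed gain at almost no cost. The outcome definition and the sample size agree on the end-of-treatment difference; the analysis text neither selects that contrast nor adjusts it for baseline.

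The power loss is conditional. It applies if the test is taken as condition-by-time or as a difference in change, and for the pre-to-post contrast only if r is below about 0.67. Within r = 0.3 to 0.6 it is large: 51% to 73%, against the planned 80%. The case for baseline adjustment does not need that condition, because the adjusted contrast is more precise than the change contrast at every r and gives up only about one degree of freedom against the planned t-test.

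All figures assume 45 analysed per arm, a two-sided 5% level and the scale of the SDs in the sample size section. Those SDs cannot belong to a composite score that runs from 0 to 1, so they fit the 9-point severity rating. If the composite is analysed, the percentages would need its own SDs; the algebra would be the same, with break-even at the baseline SD divided by twice the end-of-treatment SD.

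**What to change.** In the Statistical analyses section, name the between-arm difference in EuropASI severity at t = 1 as the single primary contrast. Estimate it in one of two ways, chosen in advance:

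1. a mixed model with t = 1 and t = 2 as responses, baseline EuropASI as a covariate and an arm-by-visit term; or
2. a mixed model with all three visits as responses and a common baseline mean across the arms. This form needs baseline among the responses.

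Report the t = 2 difference from the same model as secondary. Say that the t-test and Mann-Whitney sentence does not define the primary test.

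The cost is model wording and about one degree of freedom. Baseline EuropASI is already scheduled, so no patients, visits or data are added.

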### European addition severity index (EuropASI)

The EuropASI is the European adaptation of the fifth edition of the addiction severity index [38]. It is a semi-structured interview that gives a multidimensional profile of the substance-dependent individual and the severity of the addiction. It covers seven main problem areas (medical, employment, alcohol, drug, legal, psychiatric, and family and social) that are most commonly affected by substance abuse. Scoring is based on two indices for each problem area: firstly, the interviewer’s severity rating, in which the interviewer indicates the severity of the patient’s problems and his or her present need for additional treatment on a 9-point scale. Secondly, a composite score (range 0 - 1), an arithmetically based indicator of current (30 day) problem severity, is obtained. Composite scores for the EuropASI are computed with a strategy similar to the one used in the ASI [39].

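### The sample size is calculated on a scale that the declared primary outcome, the 0–1 EuropASI composite, cannot take, and the analysis section does not say which EuropASI index is tested

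*Protocol article*

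**What the plan says.** Four sections of the protocol article bear on this.

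- **Instruments and outcome** sets the construct and time point: "The primary outcome in this study is substance use severity at end of treatment as measured with the EuropASI". It then names the index: "The composite score for alcohol use severity will be used as the primary outcome measure for patients with alcohol use disorder", with the drug composite for the remaining patients. Each patient therefore contributes one diagnosis-specific domain.
- **The EuropASI section** describes two indices per problem area. One is "the interviewer’s severity rating, in which the interviewer indicates the severity of the patient’s problems" together with the "present need for additional treatment on a 9-point scale". The other is "a composite score (range 0 - 1), an arithmetically based indicator of current (30 day) problem severity".
- **Sample size calculation** says that it concerns the primary outcome variable. It starts from inpatient data in which "a mean baseline score of 5.2 was found for the alcohol domain and 4.0 for the drugs domain" and averages the two domains to 4.6 (SD 2.7). It plans with a baseline of 4.0 and end-of-treatment means of 1.6 (intervention) and 2.8 (control), each with SD 2.0. The result is 45 per group.
- **Statistical analyses** plans a mixed model for differences between the conditions over time "in severity of substance use problems as measured by the EuropASI severity score (pre, post and follow-up", and lists t-tests or Mann-Whitney tests for continuous variables in general.

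No section converts one index to the other or gives a mean, SD or expected difference for the composite.

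**The concern.** The outcome section and the sample size section both speak of the primary outcome, but their numbers cannot belong to the same variable. They differ in scale (0 to 1 against values from 1.6 to 5.2) and in construction (one domain per patient against the average of two). The 80% power then rests on a variable other than the declared endpoint.

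The analysis section adds a second uncertainty. The EuropASI section uses the label *severity score* for neither index. The two indices are built differently: one is an interviewer's judgement of severity and treatment need, while the other is computed from items such as days of use and money spent. They can give different answers on treatment effect. If the tested variable is not named, there is room to choose between them once the data are seen. The choice also reaches the cost-effectiveness analysis, which takes the primary outcome as its effect measure.

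**Working it through.** **1. Reproduce the stated sample size.** Inputs from the sample size section: means 1.6 and 2.8, SD 2.0, alpha 0.05, power 80%, ratio 1:1. A two-sided test is assumed, since sidedness is not stated.

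- Intervention mean: 4.0 × (1 − 0.60) = 1.6.
- Difference: 2.8 − 1.6 = 1.2. Standardised difference d = 1.2/2.0 = 0.60.
- Normal approximation: n = 2 × (1.960 + 0.842)² / 0.60² = 43.6, so 44 per group.
- Noncentral t: power is 79.5% at 44 per group and 80.4% at 45.

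The stated 45 per group is correct for these inputs.

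**2. Check the inputs against the declared scale.** The composite lies between 0 and 1.

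- Its mean must lie between 0 and 1. The planning means (5.2, 4.0, 4.6, 2.8, 1.6) all exceed 1.
- For a variable on 0 to 1 with mean m, SD ≤ √(m(1 − m)), which is largest at m = 0.5, giving 0.5. The planning SDs are 2.7 and 2.0.
- The largest possible difference between two groups is 1. The planned difference is 1.2.

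None of these values is possible for the composite. All are possible on the 9-point rating, the only other index described.

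**3. Check the domain.** The planning values are for (5.2 + 4.0)/2 = 4.6, an average over alcohol and drugs, lowered to 4.0 for outpatients. The declared outcome uses the alcohol or the drug domain, not their average. This mismatch would remain even if the scale were corrected.

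**4. What 45 per group gives on the composite.** Power depends only on d, which the article does not give for the composite. The values of d below are assumptions (two-sided t-test for power; normal approximation for n).

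| Assumed d | Power at 45 per group | n per group for 80% |
|---|---|---|
| 0.3 | 29.1% | 175 |
| 0.4 | 46.7% | 99 |
| 0.5 | 65.0% | 63 |
| 0.6 | 80.4% | 44 |
| 0.7 | 90.7% | 33 |
| 0.8 | 96.4% | 25 |

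**5. What d = 0.60 means in composite points.** Difference = 0.60 × SD. For assumed composite SDs of 0.15, 0.20, 0.25 and 0.30 this is 0.09, 0.12, 0.15 and 0.18. With the SD at its ceiling of 0.5 it is 0.30. Conversely, an assumed difference of 0.10 gives power of 87.9% with SD 0.15, 65.0% with SD 0.20 and 46.7% with SD 0.25.

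**The case against.** Several stronger readings are tempting, and the article does not support them.

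- *That the mixed model tests the 9-point interviewer rating.* The analysis section does not say so. The EuropASI section calls the interviewer index a rating and calls the composite a score that indicates problem severity, and the outcome section also describes the composite in terms of use severity. The label could be shorthand for the composite. The scale used for the sample size points the other way but does not settle it. What stands is that the label is ambiguous.
- *That the declared endpoint goes untested.* The same section also provides for t-tests or Mann-Whitney tests of continuous variables, so a comparison of the composite at end of treatment is not excluded.
- *That there are two rival primary outcomes.* The outcome section names one, by instrument, index, domain and time point. No section calls the interviewer rating primary.
- *That the trial is underpowered.* If d = 0.60 carried over to the composite, 45 per group would still be right, and a larger d would give more power. No loss can be derived from the article.

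It might also be said that a full protocol or analysis plan would settle these details. That answers a gap, not a conflict: the article itself states the index, its range and the planning values, and they cannot all be true of one variable.

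**Conclusion.** The point holds for the sample size without any outside figure. The planning means, SDs and difference are impossible on the 0–1 composite that is declared primary, and they refer to an average of two domains where the outcome uses one. So 80% power with 45 per group is not established for the declared endpoint. It holds only on the condition that the composite's standardised difference is also about 0.60, which the article neither states nor justifies. The size of any error is unknown: the 29% to 96% range comes from assumed values of d, and the equivalents in composite points come from assumed SDs.

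For the mixed model the conclusion is narrower. The analysis section does not clearly name the declared index, and this leaves some room for a choice after the data are seen.

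**What to change.** 1. In Statistical analyses, replace *EuropASI severity score* with *EuropASI composite score (alcohol or drug, according to diagnosis)*, so that the model tests the variable named in Instruments and outcome.
2. In Sample size calculation, do one of the following:
   - restate the mean, SD and expected difference in composite units for the diagnosis-specific domain, and recalculate; or
   - state that 45 per group gives 80% power only for a standardised difference of 0.60, say what that is in composite points, and give the SD used for the conversion.

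The change is to wording, plus a short recalculation if the first option is taken. Both indices come from the same interview, so no new data are collected. The price is that the power statement becomes conditional or changes, in either direction; under the first option the target number may change with it.
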